### Study design

2.1

This is a single-center, assessor-and-statistician-blinded, randomized, sham acupuncture-controlled clinical trial. The study aims to evaluate the efficacy and safety of acupuncture therapy, featuring acupoint combination for “simultaneous treatment of phlegm and blood stasis,” in treating ischemic stroke patients with hemiplegia. The study has been registered on itmctr.ccebtcm.org.cn (Registration No. ITMCTR2025001171). SPIRIT checklist is shown in Supplementary file 1.

The study will recruit 70 eligible ischemic stroke patients with unilateral limb dysfunction who meet the inclusion criteria. After signing informed consent, the participants will be randomized into acupuncture group or sham acupuncture group in a 1:1 ratio. All participants will receive a two-week treatment. Basic information will be collected before treatment (Day −1 to 0), and electroencephalogram (EEG) examination and scale evaluation will be conducted before (Day −1 to 0) and after the two-week treatment (Day 15). Allocation information will be confidential to assessors. The study process is shown in Figure 1 and the timeline for enrolment, intervention and assessment is shown in Table 1. The study will be started in June 2025 and complete recruitment by June 2028. The entire study is expected to be finalized by December 2028.

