##### EEG data collection

2.12.2.6

Patients will undergo EEG examination before and after treatment, respectively. EEG recording will be conducted in a dimly lit and quiet environment to avoid visual and auditory distractions. Patients are required to avoid caffeinated beverages, sedatives, and stimulants for three days prior to the examination. They should also ensure 7.5 h of sleep before the test and avoid fatigue, hunger, and hypoglycemia. During the examination, they should stay conscious, keep their eyes closed, remain relaxed, and refrain from feeling tense or anxious. The study will employ the 32 U-type digital electroencephalogram/brain electrical activity mapping (EEG/BEAM) instrument, with electrodes placed according to the international 10–20 system (refer to Figure 4). In the unipolar lead method, bilateral earlobes (A1, A2) are selected as the reference electrodes to record the potential difference between the active electrodes and the reference electrodes. The lead arrangement is as follows: FP1-A1, FP2-A2, F3-A1, F4-A2, C3-A1, C4-A2, P3-A1, P4-A2, O1-A1, O2-A2, F7-A1, F8-A2, T3-A1, T4-A2, T5-A1, T6-A2. The bipolar lead method records the potential difference between two adjacent electrodes, anterior and posterior, in symmetrically paired regions of the left and right hemispheres. The lead arrangement is as follows: FP1-F3, F3-C3, C3-P3, P3-O1, FP2-F4, F4-C4, C4-P4, P4-O2, FP1-F7, F7-T3, T3-T5, T5-O1, FP2-F8, F8-T4, T4-T6, T6-O2. Parameter settings: sensitivity 10 μv/mm, time base 30 mm/s, time constant 0.3, high-pass filter 70 Hz, low-pass filter 0.53 Hz. Routine eye-opening/closing evoked test will be conducted during recording, with a duration of 20 min. An independent researcher will analyze EEG data, calculating the frequency and amplitude of background brainwave patterns in each hemisphere and abnormal waveforms in lesioned regions. EEG data will be collected using the XLTEK neuroworks EEG system.

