##### Coherence analysis

2.12.2.8

Coherence is an index used in EEG analysis to measure signal synchrony between two brain regions, reflecting the degree of functional connectivity between them. The coherence C*_xy_* (*f*) between two EEG signals *x* and *y* from different electrodes at frequency *f* is calculated using the following formula:

$$C_{\mathrm{xy}}(f)=\frac{|P_{\mathrm{xy}}(f)|2}{P_{\mathrm{xx}}(f).P_{\mathrm{yy}}(f)}$$

*P_xx_* (*f*) and *P_yy_* (*f*) represent the power spectral densities of signals *x* and *y*, respectively, while *P_xy_* (*f*) is the cross-spectral density between *x* and *y*, all of which are estimated using the Welch method. Coherence ranges from 0 to 1, with higher values indicating greater similarity in phase and amplitude between EEG signals, among which, a value of 1 indicates complete synchronization, while 0 indicates complete desynchronization. This study will calculate coherence in the alpha and beta bands, designating the M1 region (primary motor cortex) on the ipsilesional or contralesional side of the lesion as the seed region, and will calculate coherence values between the seed region and all other regions. In the 32-electrode layout of the international 10–20 system, the M1 seed region is defined as C3 (for the left hemisphere M1) or C4 (for the right hemisphere M1). When the infarct lesion is located in the right hemisphere, the data will be flipped along the midline to standardize the analysis hemisphere. For normally distributed data, two independent-samples t-test will be conducted, while for non-normally distributed data, non-parametric Wilcoxon test will be applied to compare Coherence differences between the two groups. Additionally, Cohen’s *d* will be calculated to quantify the effect size, and the Bonferroni correction will be employed to control the false positive rate associated with multiple comparisons.

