### Statistical analysis

2.16

All data will be analyzed using SPSS 27.0 statistical software. In accordance with the intention-to-treat (ITT) principle, patients who have received at least one treatment session will be included in the analysis. Basic information, baseline data, and efficacy evaluation will be analyzed using both the full analysis set (FAS) and per-protocol set (PPS). In case of inconsistent results between the two datasets, further analysis and evaluation will be conducted. Missing data will be imputed using multiple imputation method. For continuous outcomes, post-treatment data are presented as mean±SD if normally distributed with equal variances; otherwise, they are presented as median (IQR). ANCOVA will be used to adjust for baseline values and confounders (e.g., age, gender, revascularization therapy status), with adjusted mean differences and 95% CIs reported. For categorical data, frequencies and percentages will be presented, and potential confounders will be screened via univariate analysis before constructing stepwise logistic regression models to adjust for confounders and report odds ratios with 95% CIs, followed by validation of the model’s goodness of fit. Further, patients will be grouped based on infarction location to analyze EEG indicators in each subgroup. Receiver operating characteristic (ROC) curve analysis will be conducted to evaluate the predictive value of EEG as an efficacy indicator for acupuncture response, with the area under the curve (AUC) and 95% CI reported. For correlation analysis, Pearson correlation will be applied to normally distributed continuous data, while Spearman correlation will be used for ordinal data. All data analysis will be conducted using two-tailed tests with a significant level of 5%.

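### Section 2.12.2.8 tests EEG coherence with no baseline term while 2.16 prescribes baseline-adjusted ANCOVA, and the electrode count and seed leave the Bonferroni family anywhere from about 30 to 124 tests

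*Protocol article*

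**What the plan says.** **Data.** Section 2.1 states that "electroencephalogram (EEG) examination and scale evaluation will be conducted before" treatment, and again on Day 15. Each patient with both recordings therefore has a baseline coherence for every electrode pair.

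**Test.** Section 2.12.2.8 says: "For normally distributed data, two independent-samples t-test will be conducted". Otherwise a "non-parametric Wilcoxon test will be applied to compare Coherence differences between the two groups". Neither test carries a covariate, and the quantity compared is not defined.

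**General rule.** Section 2.16, on continuous outcomes, says: "ANCOVA will be used to adjust for baseline values and confounders". Coherence is continuous, is listed under secondary outcomes, and is not excepted.

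**Multiplicity.** Section 2.12.2.8 says that "the Bonferroni correction will be employed to control the false positive rate associated with multiple comparisons", without a count. Coherence is computed in two bands (alpha and beta), from an M1 seed on the lesion side or the opposite side, to all remaining regions.

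**Electrodes.** Section 2.12.2.8: "In the 32-electrode layout of the international 10–20 system, the M1 seed region is defined as C3" or C4. Section 2.12.2.6 lists these unipolar leads: "FP1-A1, FP2-A2, F3-A1, F4-A2, C3-A1, C4-A2, P3-A1, P4-A2, O1-A1, O2-A2, F7-A1, F8-A2, T3-A1, T4-A2, T5-A1, T6-A2". It lists these bipolar derivations: "FP1-F3, F3-C3, C3-P3, P3-O1, FP2-F4, F4-C4, C4-P4, P4-O2, FP1-F7, F7-T3, T3-T5, T5-O1, FP2-F8, F8-T4, T4-T6, T6-O2".

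**The concern.** Two sections prescribe different analyses for the same outcome. An analyst following 2.12.2.8 would run an unadjusted two-group test, and one following 2.16 would adjust for baseline. The first leaves unused a covariate that has already been collected.

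The Bonferroni divisor cannot be read off the text either. The number of target electrodes and the number of seeds each have two possible values. If the divisor is settled only when results are in view, the correction loses some of its force.

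Coherence is the plan's main evidence on brain connectivity as a mechanism. With about 30 patients per arm and a strict per-test level, precision is scarce.

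**Working it through.** **1. The plan's own figure.** Section 2.7 gives a standard deviation of 7.81, a difference of 6.59, α = 0.05 and power 0.90. Two-sided, n = 2 × (1.960 + 1.282)² × 7.81² / 6.59² = 29.5, so 30 per group, as stated. Then 30 × 1.15 = 34.5, so 35 per group and 70 in total. The plan's figure is reproduced. No sample size or power is stated for coherence, so 30 per arm is used below.

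**2. What baseline adjustment is worth.** Let r be the pre-post correlation of coherence for one pair. The documents do not give it, so 0.5 to 0.8 is an assumption. Relative to the variance of a Day 15 comparison (set to 1), a change score has variance 2(1 − r) and ANCOVA has 1 − r².

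| r | ANCOVA / Day 15 test = 1 − r² | ANCOVA / change test = (1 + r)/2 |
|---|---|---|
| 0.5 | 0.75 | 0.75 |
| 0.8 | 0.36 | 0.90 |

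ANCOVA is the more precise under either reading of what is compared.

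**3. Electrodes recorded.** The unipolar list has 16 active electrodes. The 16 bipolar derivations use the same 16 and add none.

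**4. Size of the Bonferroni family.** m = targets × 2 bands × seeds, taking each region as one electrode. The per-test level is 0.05/m. The detectable standardised difference d solves P(T > t) = 0.80, where T is noncentral t with 58 degrees of freedom and noncentrality d × √(30/2), and t is the two-sided critical value at 0.05/m.

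| Reading | m | Level per test | Detectable d, 80% power | Power at an assumed d of 0.8 |
|---|---|---|---|---|
| Single test, for reference | 1 | 0.05 | 0.74 | 86% |
| 16 electrodes, 1 seed: 15 × 2 × 1 | 30 | 0.00167 | 1.08 | 43% |
| 16 electrodes, 2 seeds: 15 × 2 × 2 | 60 | 0.00083 | 1.13 | 35% |
| 32 electrodes, 1 seed: 31 × 2 × 1 | 62 | 0.00081 | 1.14 | 34% |
| 32 electrodes, 2 seeds: 31 × 2 × 2 | 124 | 0.00040 | 1.20 | 27% |

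With two seeds the C3–C4 pair occurs twice; counted once, m is 58 or 122. The electrode mismatch multiplies m by 31/15 = 2.07 and the seed choice by 2, about fourfold together (124/30 = 4.1).

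**5. Which cause does most.** Correction alone raises d from 0.74 to between 1.08 and 1.20. Adjustment then multiplies a Day 15 d by √(1 − r²). At r = 0.5 the factor is 0.866, so 1.075 becomes 0.93 and 1.195 becomes 1.03 to 1.04. At r = 0.8 the factor is 0.6, giving 0.65 and 0.72. With the electrode count changed from 16 to 32 and the seeds fixed, d moves only from 1.08 to 1.14 (one seed) or from 1.13 to 1.20 (two seeds).

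**The case against.** Several stronger readings are tempting, and the documents do not support them.

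- **That baseline coherence is ignored by design.** This is not stated. The difference compared in 2.12.2.8 could be a change, the Discussion frames the aim as change over the treatment period, and 2.16 prescribes baseline adjustment. What stands is that the two sections disagree and the compared quantity is undefined.
- **That most of the precision is thrown away.** That needs the Day 15 reading and 1 − r² below 0.5, which means r above about 0.71. Against a change score the saving is 10–25%. In a randomised comparison the unadjusted test is not biased.
- **That the missing baseline explains the large detectable effects.** Bonferroni explains most of it: at r = 0.5, ANCOVA still needs about 0.93 to 1.04. The planning value for the primary outcome, 6.59/7.81 = 0.84, belongs to a different outcome at 90% power and is a loose yardstick. A null coherence result would be weakly informative, not empty, since 2.12.2.8 also reports Cohen's d.
- **That the electrode mismatch alone makes the family uncountable.** The open choice of seed side doubles it as well, and regions are not mapped to electrodes.

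It can also be said that 32 may come from the instrument's designation in 2.12.2.6, and that an exact count belongs in an analysis plan that is not shown. Both are possible. Neither removes the conflict between the printed sections: 2.12.2.8 presents 32 as the layout in which the seed is defined, and 2.12.2.6 lists 16 electrodes. Finally, coherence is exploratory mechanistic work, which limits how much depends on it.

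**Conclusion.** The point holds as two modest defects.

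First, 2.12.2.8 and 2.16 give different analyses for coherence, and the former omits a baseline already collected. The cost is precision, not validity. ANCOVA would have 36–75% of the variance of a Day 15 test, or 75–90% of that of a change-score test, if the pre-post correlation is 0.5 to 0.8. That range is assumed.

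Second, the stated 32 electrodes conflict with the 16 listed, and the seed side is left open. The Bonferroni family is thus about 30 to 124 tests, with detectable d from 1.08 to 1.20 at 80% power and 30 per arm, before adjustment. The electrode conflict by itself changes detectable d by only about 0.06.

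The primary outcome, its analysis and the sample size of 70 are untouched. This is worth correcting as a free improvement, and does not threaten the trial's main conclusion.

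**What to change.** In section 2.12.2.8:

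1. Replace the t-test/Wilcoxon rule with ANCOVA of Day 15 coherence on arm and the same electrode pair's baseline coherence, in line with 2.16. If a transformation is needed, choose one suited to magnitude-squared coherence, which is what the printed formula gives; a Fisher z does not apply to it directly.
2. Reconcile the 32 electrodes with the 16 listed in 2.12.2.6, by correcting the number or listing the further leads.
3. State whether the seed is the ipsilesional M1, the contralesional M1 or both, and which electrodes count as the other regions.
4. State the resulting number of tests and apply Bonferroni with it. For example, 16 electrodes, one seed and two bands give 30. A permutation correction is an option but is not needed to cure the defect.

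The cost is a few sentences and slightly more analysis code. No new data or patients are needed, and the article reports that the trial is still recruiting.

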Rehabilitation therapy is the primary method to restore impaired limb function in stroke patients by enhancing neuronal activities, increasing postsynaptic excitability, and promoting the regeneration of dendritic spines and the recovery of myelin sheaths (3). The conventional rehabilitation for stroke primarily includes neuromuscular electrical stimulation, physical therapy, occupational therapy, and rehabilitation robots (4). However, the high cost and cumbersome training methods make it difficult for patients to adhere to the therapy in long term, thus presenting limited effectiveness (5). In China, acupuncture experienced a long history over 2,000 years and has been widely applied in the treatment of limb dysfunction after stroke (6). Owing to its simplicity of operation, effectiveness, and safety, acupuncture may serve as an alternative for improving post-stroke sequelae with minimal adverse effects (7). Studies have suggested that acupuncture, as a form of somatosensory stimulation, can induce plastic changes among different representations in the motor cortex, modulate interhemispheric competitive inhibition, and improve cerebral cortical function (8, 9). Acupuncture applied to the unilateral limb can stimulate neuronal excitability in bilateral brain regions, increase cerebral blood flow, and enhance the consistency of neuronal activity in the motor area of the affected hemisphere (10). It has been reported that bilateral needling method of hand-foot 12 needles can improve the motor recovery post-stroke and modify cerebro-cerebellar voxel-mirrored homotopic connectivity (11). Scalp acupuncture therapy combined with exercise therapy can significantly improve stroke patients’ ability to participate in daily activities (12). However, the acupoint selection in these studies has failed to integrate with the pathogenic characteristics of stroke in TCM, thus not fully leveraging the advantages of syndrome differentiation in acupoint selection. Moreover, the mechanisms underlying the therapeutic effects of acupuncture for hemiplegia remain unclear, lacking the support of objective evidence, which limits the development and application of acupuncture in stroke rehabilitation to some extent.

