### Sample size calculation

2.7

Sample size for this study is estimated according to the formula for the comparison of means in a randomized controlled trial. Referring to the relevant literatures (26, 27), we estimate the pooled standard deviation (*σ*) of the treatment group and the control group to be 7.81, and the difference between the means of the two groups (*δ*) to be 6.59. We set the significant level (*α*) at 0.05, the Type II error rate (*β*) at 0.1, and the statistical power (1-β) at 0.9. After substituting the values into the formula, calculated sample size per group requires 30 cases. Considering a 15% dropout rate, a total of 70 cases will be enrolled.

$$n=\frac{2{\left(z_{\alpha }+z_{\beta }\right)}^{2}*\sigma^{2}}{\delta^{2}}$$

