
Outcome measures include the simplified Fugl-Meyer Assessment for motor function, the Berg Balance Scale, the Fugl-Meyer Assessment for sensory function, the Modified Ashworth Scale, the Modified Barthel Index, and TCM syndrome scoring scale, which are used to comprehensively evaluate the efficacy of the “simultaneous treatment of phlegm and blood stasis” acupuncture therapy based on syndrome differentiation on improving limb mobility, balance, sensation, muscle tone, activities of daily living, and TCM-related symptoms/signs in ischemic stroke patients with hemiplegia. Resting-state EEG is highly sensitive to cerebral metabolic and neurological functional abnormalities, serving as an important method for assessing post-stroke brain function (38). Commonly used frequency bands in EEG include alpha, beta, theta, and delta waves. Alpha wave activity during rest reflects the level of consciousness and visual attention (39). With a frequency range of 8–13 Hz, alpha waves are brain rhythms involved in various functions, ranging from sensorimotor processing to memory formation (40). Research indicates a linear relationship between reduced synchrony of alpha wave oscillations among brain regions and cognitive/motor function impairments in stroke patients (41). Beta waves, oscillating at 13–30 Hz, are crucial rhythms in cortical activity, closely related to motor control and sensorimotor integration (42), with their generation involving the synergistic action of pyramidal and inhibitory neurons (43). Research has found that beta wave coherence can serve as a marker for cortical functional plasticity after stroke (42). Delta waves are low-frequency waves with frequencies ranging from 1–4 Hz, and can be detected during slow-wave sleep and execution of cognitive tasks (44). Theta waves, with frequencies in the 4–8 Hz range, have been extensively studied in emotional and cognitive domains. Recent research has found that perturbation during seated movements can evoke differential theta-band responses in the anterior cingulate cortex and supplementary motor areas (45). In this study, we will employ EEG to record and analyze the frequency, amplitude, and spectral power of delta, theta, alpha, beta waves. We will designate the M1 region as the seed region and calculate the coherence of alpha and beta waves between the seed region and other regions. By observing changes in neuronal oscillation frequencies, electrical activity intensity, and functional connectivity across different brain regions before and after treatment, we aim to explore the neurophysiological mechanisms, by which acupuncture improve limb function in stroke patients, and screen EEG-based biomarkers with predictive value.

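### Plain Bonferroni on the M1-seed coherence tests is valid but needlessly conservative; a step-down max-T permutation test holds the same 5% and recovers some power for focal effects

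*Protocol article*

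**What the plan says.** Section 2.12.2.8 (Coherence analysis) takes C3 or C4 as the M1 seed and "will calculate coherence values between the seed region and all other regions", in two bands. Each value is compared between arms by a two-sample t-test, or by a Wilcoxon test if the data are not normal. Cohen's d is reported, and "the Bonferroni correction will be employed to control the false positive rate associated with multiple comparisons". No pair or band is ranked above another.

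The section does not give the number of regions, say whether one or both seeds enter the same family, or say whether the bands are corrected together. A journal article can leave such detail to the full protocol, so that is not the point here. The choice of plain Bonferroni, however, is fixed in the text.

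The sample size (section 2.7) rests on the Fugl-Meyer score alone, with "the statistical power (1-β) at 0.9". The document gives no effect size or power for coherence.

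**The concern.** All these coherence values come from the same recording and share the seed signal, and neighbouring electrodes pick up overlapping activity. Positive correlation between the tests is therefore likely. Bonferroni is safe under any dependence, and the price is that under positive correlation it spends less than the 5% it is allowed. Methods that use the correlation hold the same family-wise guarantee and reject more.

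Functional connectivity is one of the two things the abstract says the EEG will evaluate, the other being cortical excitability. If acupuncture changed coherence at one pair only, the stated rule would miss it more often than it needs to.

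**Working it through.** **Inputs from the document**
- Level: 5%, two-sided (section 2.16: "All data analysis will be conducted using two-tailed tests with a significant level of 5" per cent).
- SD "of the treatment group and the control group to be 7.81"; "the difference between the means of the two groups (*δ*) to be 6.59" (section 2.7). So d = 6.59/7.81 = 0.844. This is the Fugl-Meyer effect, used here only as a benchmark.
- 30 evaluable per arm; 70 enrolled, so 35 per arm with no dropout.
- 16 referential leads listed in section 2.12.2.6.

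**Inputs assumed**
- Family size. One seed against the other 15 leads gives 15 tests if each band is its own family, and 15 × 2 = 30 if both bands are pooled.
- Correlation between coherence values within a band of 0.3 to 0.8.

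**Step 1: the plan's own figure.** n = 2(1.960 + 1.282)² × 7.81²/6.59² = 29.5, so 30 per arm, as stated. Exact noncentral-t power at 30 per arm (df = 58) is 89.5%.

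**Step 2: power for one affected pair under Bonferroni.** Each test is made at 0.05/m. The noncentrality is d√(n/2), which is 3.268 for n = 30 and 3.530 for n = 35.

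| Tests (m) | Level per test | Critical t, n = 30 | Power, 30 per arm | Power, 35 per arm |
|---|---|---|---|---|
| 1 | 0.0500 | 2.002 | 89.5% | 93.6% |
| 15 | 0.0033 | 3.062 | 58.4% | 68.5% |
| 30 | 0.0017 | 3.298 | 49.4% | 60.2% |

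Larger families are possible. Both seeds on the 16 leads give (15 + 14) × 2 = 58 tests and 41% power at 30 per arm. The 32-electrode layout mentioned in section 2.12.2.8 gives 31 × 2 = 62 tests and 40.5%. The effect detectable with 80% power at 30 per arm rises from d = 0.74 (one test) to 1.08 (30 tests).

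**Step 3: how conservative Bonferroni is, and what max-T recovers.** Null trials were simulated with 30 per arm, 30 tests, two bands and normal data. The 95% point of the largest |t| replaces 3.298 as the cut-off, and per-pair power is recomputed at that cut-off. This is the single-step version; step-down is at least as powerful.

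| Correlation within / between bands | True family-wise error of Bonferroni | Max-T cut-off | Power with max-T (Bonferroni 49%) |
|---|---|---|---|
| 0.3 / 0.2 | 4.6% | 3.27 | 50% |
| 0.5 / 0.3 | 3.7 to 4.3% | 3.18 to 3.23 | 52 to 54% |
| 0.7 / 0.4 | 2.7 to 2.8% | 3.06 to 3.07 | 58 to 59% |
| 0.8 / 0.5 | 2.0 to 2.5% | 2.91 to 2.95 | 62 to 64% |

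Ranges are the spread over repeated simulation runs.

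**Step 4: Holm.** In simulation with 30 equally correlated tests, per-pair power stayed at 49% with one affected pair. It rose to about 50% with five and 51 to 52% with ten. Over the settings examined the gain is 0 to 4 points.

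**Step 5: effects that are not focal.** With 5 of 30 pairs affected at d = 0.844 and 30 per arm, Bonferroni flags at least one of them in about 90% of trials at correlation 0.3, 84% at 0.5, 76% at 0.7 and 71% at 0.8.

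**The case against.** The strongest reply is that nothing here is an error. Bonferroni controls family-wise error under any dependence, coherence is a secondary measure that the Discussion describes as exploring mechanisms, and preferring a sharper valid test is a matter of efficiency. That stands, and it sets the grade of this point: a cheap improvement, not a defect.

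Three stronger readings are tempting, and the document does not support them.

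- A reader might infer that Bonferroni itself takes power from 90% to 49%. Most of that fall comes from making 30 tests at this sample size. At correlation 0.5, max-T returns only about 3 to 4 of the roughly 40 points lost.
- A reader might infer that a real connectivity effect will often be reported as absent, or that a negative result is uninformative. That goes too far. Step 5 shows that an effect over several pairs is usually flagged at some site, and section 2.12.2.8 reports Cohen's d alongside the tests, so a non-significant pair need not be read as no effect.
- A reader might infer that the protocol has already committed to interhemispheric M1 coherence in the beta band, and should test it first. The Introduction's "modulate interhemispheric competitive inhibition" summarises earlier literature and names no electrode pair or band. The Discussion does say "Research has found that beta wave coherence can serve as a marker for cortical functional plasticity after stroke", but it also links reduced alpha synchrony to motor impairment. Ranking the bands equally is consistent with that rationale.

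It is also fair that the benchmark effect and the correlations are not from the document, and that a floor of 30 tests cannot be read from it. What remains is that correlation is likely, and that a rule with the same guarantee and more power is available for little effort.

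**Conclusion.** The point holds as an inefficiency confined to focal effects. With 15 to 30 tests, 30 to 35 per arm and d = 0.84, power for a single affected pair under the stated rule is 49 to 69%; families larger than 30 would lower it. Over 30 tests Bonferroni uses about 4% of its 5% at correlation 0.5 and 2 to 3% at 0.7 to 0.8. The avoidable part of the loss is small up to correlation 0.5 (about 1 to 4 points) and material only at 0.7 to 0.8 (about 9 to 15 points).

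These sizes depend on the borrowed Fugl-Meyer effect, the inferred family and the assumed correlations. The direction does not: Holm never rejects less than Bonferroni, and step-down max-T is essentially never less powerful.

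**What to change.** In section 2.12.2.8, replace Bonferroni by a step-down max-T permutation test. Permute the arm labels, use one test statistic for all pairs, and take the maximum over the listed set of pairs and bands. Family-wise error stays at 5%.

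At minimum, use Holm. It carries the same guarantee under any dependence and can be done by hand, but it gains little (0 to 4 points) and almost nothing if only one pair is affected.

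Naming one key coherence contrast before unblinding is optional. If the sponsor does so and tests it at the full 5%, the remaining pairs may be tested only after it succeeds. The choice of pair and band is the sponsor's.

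Cost: a change of wording and, for max-T, a short script outside the standard SPSS menus. No new data are needed. Max-T gives adjusted p-values but no simple simultaneous intervals, so Cohen's d should still be reported for every pair.
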